## Abstract

**Background:**

Malnutrition, a leading cause of mortality and morbidity in children aged <5 years, requires early detection and intervention. In Ayurveda, “Kumarasosha” closely corresponds to childhood malnutrition, with its pathophysiology and treatment principles offering a more precise and effective approach to management.

**Objective:**

This study is designed to evaluate the efficacy and safety of *Ayush Bala Rakshak (BR) Leham* in moderately malnourished children aged 3 to 5 years.

**Methods:**

This is a multicenter, open-label, randomized controlled, 2-group pilot study designed to enroll 200 moderately malnourished children, 100 from each participating study center of the Central Council for Research in Ayurvedic Sciences. The children will be screened for moderate malnutrition using the World Health Organization weight-for-age *Z* score through the AnthroCal app developed by the All India Institute of Medical Sciences, New Delhi. After obtaining consent from parents, the participants will be randomized and allocated to 2 groups. The study group will receive *Aravindasava*, 5 mL twice daily after food for 4 weeks, followed by *Ayush BR Leham*, a nutritional supplement, 5 g twice daily before food from weeks 5 to 12. The control group will receive *Aravindasava* for 4 weeks and thereafter receive no intervention for 8 weeks. Both groups will be advised to follow a home-prepared diet during the study period. A follow-up assessment will be conducted after 4 weeks. The primary outcome is a change of ≥0.5 in the World Health Organization weight-for-age *Z* scores, and the secondary outcomes are changes in anthropometric measurements, the frequency of illnesses assessed using a predesigned table, and safety parameters assessed using biochemical measures.

**Results:**

The study received funding in March 2023. Participant enrolment commenced on December 16, 2023 and has been completed. After data analysis, the study findings are expected to be submitted for publication in December 2026.

**Conclusions:**

The study will investigate the efficacy and safety of *Ayush BR Leham* in moderately malnourished children aged 3 to 5 years. If the intervention is found to be effective, the findings may help incorporate Ayurvedic guidelines into standard treatment protocols for children with moderate malnutrition.

**Trial Registration:**

Clinical Trials Registry of India CTRI/2023/07/055188; https://tinyurl.com/3arpbecm

**International Registered Report Identifier (IRRID):**

DERR1-10.2196/93718

## Introduction

### Background and Rationale

Malnutrition remains one of the leading public health challenges worldwide, particularly affecting children aged <5 years. In India, the prevalence of malnutrition continues to be high despite significant economic growth and the implementation of various national nutritional programs. According to the National Family Health Survey (NFHS-4, 2015-2016), 38.4% of children aged <5 years were stunted, 35.7% were underweight, and 21% were wasted [1]. Regional data further indicate that the prevalence of underweight status ranges from 39% to 75% [2]. Malnutrition in children arises from multiple factors, such as inadequate dietary intake, frequent infections, poor sanitation, lack of access to quality health care, and suboptimal infant and young child feeding practices. It impairs immune function, increases vulnerability to infections, and results in long-term deficits in physical and cognitive development [3]. Malnutrition is also a significant contributor to mortality among children aged <5 years, accounting for more than one-third of deaths in this age group [4]. Early identification and timely intervention are crucial for improving outcomes in affected children.

Ayurveda offers a holistic and well-structured understanding of pediatric nutritional disorders. Conditions such as *Kumarasosha*, *Phakka*, *Parigarbhika*, and *Karshya* describe states of compromised nutrition in children, in which the key pathophysiological mechanisms, such as *Agnimandya* (impaired digestion and metabolism) and *Srotorodha* (obstruction in body channels), lead to *Dhatu Sosha* (undernourishment of body tissues) [5-8]. The Ayurvedic approach to managing such conditions emphasizes the correction of *Agni* and the clearing of *Srotas* (body channels) using *Deepana* and *Pachana* (digestive stimulants and carminatives). This is followed by *Brimhana* therapy (nourishment) to promote healthy tissue development [9]. Restoration of *Dhatu Parinama* (tissue transformation) ultimately enhances *Ojas*—the essence of vitality and immunity—thereby ensuring better resistance to disease and supporting optimal growth and development in children [10]. Ayurveda has a diverse pharmacopoeia of single and compound formulations tailored to specific age groups. Pediatric formulations are designed not only for efficacy but also for palatability and compliance. Dosage forms such as *Avaleha* (herbal jams) and *Asava* (fermented herbal decoctions) are commonly used in children. *Aravindasava*, an *Asava* preparation with *Deepana* and *Pachana* properties, is frequently prescribed in pediatric care as a corrective therapy for *Agnimandya*.

Although various national-level interventions are in place, undernutrition in Indian children remains a significant public health burden [2]. Ayurveda, with its individualized and holistic approach, offers promising alternatives or complementary strategies for managing pediatric malnutrition. *Ayush Bala Rakshak (BR) Leham*, formulated based on classical Ayurvedic principles and contemporary clinical needs, has the potential to improve nutritional outcomes in moderately malnourished children. This multicenter, randomized controlled pilot study aims to evaluate the efficacy and safety of *Ayush-BR Leham* in children aged 3 to 5 years with moderate malnutrition. The findings will contribute to the evidence-based integration of Ayurveda into pediatric nutritional management protocols.

*Ayush-BR Leham* is a nutritional supplement that contains herbs with *Deepana*, *Pachana*, *Srotoshodhana* (channel-cleansing), *Brimhana*, *Anulomana* (regulating *Vata*), and *Rasayana* (rejuvenating) properties. These pharmacological actions are aimed at enhancing digestion, nutrient assimilation, and tissue nourishment, thereby contributing to improved immunity and weight gain in malnourished children. This nutritional supplement combines both light and heavy components to strike a balance between digestibility and nourishment. It is prepared by triturating powdered herbs in honey, avoiding *Agnisamparka* (direct heat) to preserve the bioactivity of the ingredients. In this study, *Aravindasava* is administered to both the intervention and control groups as a standard care measure to prime the digestive system. *Ayush-BR Leham*, administered additionally to the intervention group, is expected to enhance therapeutic outcomes by synergistically supporting digestion, absorption, immunity, and growth. Both groups are advised to maintain a nutritious home-prepared diet during the study period.

### Objective

The study’s objective is to evaluate the therapeutic efficacy and safety profile of *Ayush-BR Leham* in children aged 3 to 5 years with moderate malnutrition.

## Methods

### Trial Design

The study is planned as a multicenter, open, randomized controlled, 2-group pilot study designed to investigate the therapeutic efficacy and safety profile of *Ayush-BR Leham* in managing moderate malnutrition in children aged 3 to 5 years. After obtaining written informed consent from the parents, the participants fulfilling the inclusion criteria will be randomized and assigned to the study and control groups in a 1:1 ratio. Both the study and control groups will be administered *Aravindasava* for 4 weeks to provide an initial correction of digestive function. Then, for a period of 8 weeks, *Ayush-BR Leham* will be administered to the study group, and the control group will be followed without any intervention. Both groups will undergo a follow-up period of 4 weeks. Throughout the study, both groups will be advised to strictly follow a home-prepared diet. The study protocol is reported in accordance with the SPIRIT (Standard Protocol Items: Recommendations for Interventional Trials) guidelines. The flowchart of the study plan is shown in Figure 1 [11].

**Figure 1 figure1:**
[figure not shown]
Flowchart of the study plan. BR: Bala Rakshak; CRF: case report form; MSRARI: Maharao Shekhaji Regional Ayurveda Research Institute; NARIP: National Ayurveda Research Institute for Panchakarma; OPD: outpatient department; WHO: World Health Organization.

### Study Setting

The research study will be conducted at the outpatient department of the National Ayurveda Research Institute for Panchakarma, Cheruthuruthy, Kerala, and the Maharao Shekhaji Regional Ayurveda Research Institute, Jaipur, Rajasthan.

### Eligibility Criteria

Children aged 3 to 5 years with a weight-for-age measurement between −2 and −3 SD according to the World Health Organization (WHO) weight-for-age growth standards are included in the study. Children should be free from edema, and their parents or caregivers should be willing to provide written informed consent for their children’s participation. Children with diagnosed serious health conditions such as heart disease, lung disease, concurrent hepatic disorder, renal disorder, congenital anomalies, inborn errors of metabolism, malignancy, tuberculosis, or HIV, as well as children with acute infections, including respiratory tract infections, diarrhea, or fever, will be excluded from the study. Children with known allergies to the trial medication or its components, children who have participated in other clinical trials within the past 6 months, and children with any other condition deemed by the investigator to pose a risk to study validity will also be excluded.

### Interventions

The drug *Aravindasava* has been procured from Indian Medicines Pharmaceutical Corporation Limited, a Good Manufacturing Practice–certified pharmaceutical company in Almora, Uttarakhand, with a quality assurance certificate ensuring compliance with the Ayurveda Pharmacopoeia of India standards [12]. The trial drug *Ayush-BR Leham* was prepared at the pharmacy of the Central Ayurveda Research Institute, Kolkata, as per the standard operating procedures developed by the Central Council for Research in Ayurvedic Sciences (CCRAS). The study drugs will be stored in a dark, cool, and dry place. The investigators will administer *Aravindasava* in both groups for 4 weeks at a dose of 5 mL twice daily after food, followed by *Ayush-BR Avaleha* in the study group at a dose of 5 g twice daily before food for 8 weeks. There will be no intervention in the control group after *Aravindasava* administration.

Both groups receive *Aravindasava*, ensuring that no group is disadvantaged in the early, critical phase, during which correction of digestion, absorption, and assimilation is necessary. All participants will receive standard nutritional care and public health interventions available to the general pediatric population with malnutrition during the study period. These include regular nutritional counseling by Accredited Social Health Activist workers or *Anganwadi* workers through government initiatives, age-appropriate dietary guidance from the study pediatrician, health check-ups and monitoring by the research team, management of infectious diseases that develop during the study, immunization, and routine health care. Both groups are advised to follow a home-prepared diet throughout the study. A home-prepared diet refers to age-appropriate, nutrient-dense meals that the family provides at home following personalized dietary counseling by the study team. It represents optimized nutrition within the family’s resources and cultural context. Compliance with the home-prepared diet will be recorded in the case report form (CRF).

### Outcome Measures

The primary outcome measure is the proportion of participants attaining a change in the weight-for-age *Z* score (WAZ) by ≥0.5, as per WHO reference standards, from baseline to weeks 12 and 16. The secondary outcome measures include changes in anthropometric measurements (weight in kg, height in cm, and midupper arm circumference in cm), which will be assessed every 2 weeks for 12 weeks, followed by assessment at week 16. Change in the frequency of illnesses will be assessed at baseline, week 12, and week 16 using a predesigned table that records the frequency and duration of illnesses. Assessment of safety (complete blood count [CBC], liver function test [LFT], renal function test [RFT], and serum electrolytes) will also be performed at baseline and week 12 in a small proportion of participants whose parents provide consent.

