### Statistical Methods

The primary outcome of the study, namely, the proportion of participants achieving an improvement in the WAZ of ≥0.5, will be analyzed using an intention-to-treat approach. Between-group comparisons for the primary binary outcome will be performed initially using the chi-square test, followed by multivariate logistic regression to estimate adjusted effect sizes after controlling for important covariates, including study center, baseline, WAZ, age, sex, and other clinically relevant variables. This will be done in the following steps:

Step 1: an unadjusted between-group comparison will be performed using the chi-square test to examine the crude difference in the proportion of participants achieving the primary outcome between the intervention and control groups. This provides transparency and allows readers to evaluate the raw effect.Step 2: multivariate logistic regression will be used to estimate the adjusted odds ratio and 95% CI, while controlling for the following prespecified covariates: study center, baseline WAZ (continuous), age (months), sex, baseline nutritional status category, socioeconomic status, and educational status of parents. The adjusted analysis represents the primary analytic result and will be emphasized in reporting and interpretation.

For the secondary outcomes, within-group pre-post changes will be examined using a paired *t* test or Wilcoxon signed-rank test, as appropriate, and will be reported for descriptive purposes. For parameters assessed at multiple follow-up time points, repeated-measures ANOVA or the Friedman test will be applied to assess temporal trends. All analyses will be performed using SPSS (version 29.0; IBM Corp), and statistical significance will be assessed at α=.05 (2-tailed).

Participants who withdraw, are lost to follow-up, or do not complete the week 12 assessment will be documented, and reasons for dropout will be recorded. Dropout rates and reasons will be presented by study group in the CONSORT (Consolidated Standards of Reporting Trials) flowchart.

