The *Kashyapa Samhita*, a classical textbook of Ayurvedic pediatrics, defines “Lehana” as a formulation that is heavy to digest but nourishing and is recommended for emaciated children [18]. *Ayush-BR Leham*, the trial drug, is one such nutritional supplement. The nutrition supplied after digestion correction is expected to be properly digested and assimilated by the body, supporting healthy weight gain [19]. Studies support that intestinal dysfunction, inflammation, and environmental enteric dysfunction can impair nutrient absorption despite adequate intake from fortified foods [20]. Hence, the sequential treatment approach is conceptually robust, as it aims to optimize digestive and metabolic functions before nutritional supplementation, thereby enhancing nutrient bioavailability and assimilation [21]. Such a strategy is likely to promote more effective and sustained recovery, rather than transient weight gain alone. This study design thus offers more treatment responsiveness and reduces the likelihood of incomplete recovery observed in standard supplementation-based interventions.

This study is designed as an exploratory randomized controlled trial to evaluate the efficacy of the nutritional supplement, *Ayush-BR Leham*, in moderately malnourished children. It is hypothesized that the trial intervention will result in a clinically meaningful improvement in nutritional status, reflected by an increase of ≥0.5 in WAZ among moderately malnourished children. Additionally, the intervention is expected to improve anthropometric parameters and reduce illness frequency compared with the control group.

The study has several strengths, including a randomized controlled design, the use of standardized and clinically relevant outcome measures such as WAZ, and repeated follow-up assessments that enable evaluation of trends over time. WAZ is a well-established indicator of child mortality and is sensitive to changes associated with nutritional interventions. Previous trials have demonstrated that improvements in WAZ reflect meaningful recovery and improved clinical outcomes [22,23]. Even mild improvements in WAZ following a short-term intervention with a nutritional supplement signify a positive shift in overall nutritional status and reduced morbidity. Additionally, a *Z* score ≥0.5 exceeds the normal day-to-day variation expected due to fluctuations in hydration status, illness, or measurement errors [24].

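### Secondary growth outcomes are raw kg and cm tested only within arm and over time, so ordinary growth can make weight and height gains significant in either arm, and no between-arm comparison is named

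*Protocol article*

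**What the plan says.** - **Scale.** Outcome Measures lists, as secondary outcomes, "changes in anthropometric measurements (weight in kg, height in cm, and midupper arm circumference in cm". They are measured on a schedule "which will be assessed every 2 weeks for 12 weeks, followed by assessment at week 16". The only age- and sex-standardised growth outcome is the primary one: the proportion of children whose WAZ changes by at least 0.5 "from baseline to weeks 12 and 16".
- **Tests.** For secondary outcomes, Statistical Methods says "within-group pre-post changes will be examined using a paired" t test or a Wilcoxon signed-rank test, and that these "will be reported for descriptive purposes". For parameters measured at several visits, "repeated-measures ANOVA or the Friedman test will be applied to assess temporal trends". That sentence has no descriptive label and names no group factor. For all analyses, "statistical significance will be assessed at α=.05 (2-tailed".
- **Between-arm methods.** The chi-square test and the adjusted logistic regression are assigned to the primary binary outcome only.
- **Expectation.** Anticipated Findings states that "the intervention is expected to improve anthropometric parameters and reduce illness frequency compared with the control group".

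**The concern.** A paired test, or a test for time trend, asks whether the mean change differs from zero. For weight in kg and height in cm at this age that question is settled before the trial starts, because children grow. A significant result therefore says nothing about Leham. It does not even show that nutrition improved, since the trial defines malnutrition by distance from the WHO weight-for-age standard. A child who grows more slowly than the standard becomes more malnourished on that definition, yet still adds a positive change in kg and cm.

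The harm comes from two features together: raw units, and tests that look only within an arm. The stated expectation is comparative, but no test named for these outcomes can address it. If the plan is followed as written, both arms are likely to show significant gains in weight and height whatever the supplement does, and those gains could be read as improved anthropometry.

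**Working it through.** **1. Inputs from the document.** The Abstract gives 200 children and the allocation is 1:1, so there are 100 per arm over both centres. Sample Size allows for 20% attrition: 100 × 0.8 = 80 completers per arm. The follow-up points are day 84 and day 112.

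The protocol's own sample-size figure reproduces. For 60% v 30%, two-sided α = 0.05 and 80% power with pooled variance:

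n = [1.96·√(2·0.45·0.55) + 0.842·√(0.24 + 0.21)]² / 0.30² ≈ 42 per group, as stated.

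That figure concerns the primary outcome. The protocol gives no figure for the secondary outcomes.

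**2. Inputs assumed (not in the document).**
- Normal gain: 1.5 to 2.5 kg/year and 5 to 8 cm/year.
- SD of change: 0.4 to 0.6 kg and 0.7 to 1.2 cm.
- One WAZ unit in the −2 to −3 range: about 1.3 to 1.8 kg.

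**3. An arm that falters: half the normal rate, 112 days.**
- Weight gain = 0.5 × (1.5 to 2.5) × 112/365 = 0.23 to 0.38 kg.
- Paired t = gain / (SD/√80). The least favourable case is 0.23/(0.6/8.94) = 3.4, p ≈ 1×10⁻³. The most favourable is 0.38/(0.4/8.94) = 8.6, p ≈ 6.5×10⁻¹³.
- The shortfall against normal growth is also 0.23 to 0.38 kg. The change in WAZ is about −0.23/1.8 = −0.13 to −0.38/1.3 = −0.30.
- Height gain = 0.5 × (5 to 8) × 112/365 = 0.77 to 1.23 cm. The smallest t is 0.77/(1.2/8.94) = 5.7, p ≈ 2×10⁻⁷.

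**4. The same at 84 days.** The smallest weight gain is 0.5 × 1.5 × 84/365 = 0.17 kg. With SD 0.6 kg, t = 2.6 and p ≈ 0.012, still below 0.05.

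**5. An arm with no nutritional change (normal growth, 112 days).** The smallest gain is 0.46 kg. With SD 0.6 kg, t = 6.9 and p ≈ 1.4×10⁻⁹.

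**6. Within-arm against between-arm.** This simulation used separate assumptions: reference 12-week gain 0.4 kg, both arms gaining 0.2 kg, SD 0.5 kg, 80 per arm, 20,000 replicates.

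| Test on the same data | Result |
|---|---|
| Within-arm paired t on kg, against zero | significantly positive in 94% |
| Within-arm, against the reference gain | significantly negative in 94% |
| Between arms on kg, no true difference | rejects in 5% |

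The first row depends on the SD. For a 0.2 kg gain, power runs from about 100% (SD 0.3 kg) to 60% (SD 0.8 kg) with 80 completers, and from 98% to 34% with 40, the number left at one centre after 20% attrition of 50.

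The third row locates the fault: the same raw kg give a correctly sized test once the arms are compared.

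**The case against.** The strongest reply is that randomisation removes the problem. Ordinary growth is expected equally in both arms, so a between-arm difference in kg or cm is a valid treatment effect. This stands, and the simulation confirms it. A reader might infer that raw units are invalid for these outcomes however they are analysed. The documents do not support that. The difficulty is that the article assigns these outcomes no between-arm comparison. In a randomised contrast, standardised scores add interpretability on the scale that defines the condition; they do not rescue validity.

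Four further points have weight:
- **The pre-post tests are labelled descriptive.** True, and it softens the matter. The label does not extend to the time-trend tests, and the α = .05 statement covers all analyses.
- **Weight is already standardised through the primary outcome.** Partly. An arm losing WAZ would be expected to show few responders. But a responder proportion does not show the mean change, and height and arm circumference have no standardised counterpart among the listed outcomes.
- **Z scores alone would not cure within-arm tests.** Correct. Children are selected for WAZ between −2 and −3, and Table 1 has a single screening-or-baseline column, so regression to the mean would be expected to lift mean WAZ. Both arms also receive Aravindasava and dietary counselling. The standardised scores must be paired with a between-arm comparison.
- **The change comes late.** Enrolment is complete, the trial is open-label, and amendments need ethics approval. This favours adding outcomes over replacing the registered ones.

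A statistical analysis plan may exist and may add a group term. The point here is confined to what the article states.

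**Conclusion.** The concern holds for the combination of raw units with within-arm and time-trend tests. For weight and height, those tests can be significant in either arm, including one that is falling behind the WHO standard. They cannot answer the comparative expectation in the Discussion.

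Over the assumed ranges with 80 completers per arm, an arm at half normal growth for 16 weeks gives t of 3.4 to 8.6 for weight and at least 5.7 for height, while mean WAZ drops by about 0.13 to 0.30. Growth rates, SDs and kg per WAZ unit are all assumptions. The direction is firm; the exact p-values are illustrative. With a larger SD (0.8 kg) or only 40 completers, significance is less assured.

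Two stronger readings go too far. One is that all three measures will rise significantly: nothing here establishes how far arm circumference changes over 12 to 16 weeks. The other is that the trial will claim efficacy from within-arm gains: the article labels the pre-post results descriptive and words its expectation against control. The primary analysis is not affected. This is a correctable weakness in the secondary analysis and should be put right before the data are analysed.

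**What to change.** In Outcome Measures, keep the listed kg and cm measures and add continuous change in WAZ, height-for-age Z and arm-circumference-for-age Z on the WHO reference. BMI-for-age Z is optional, since Table 1 already lists BMI.

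In Statistical Methods, state that change in these scores is compared between arms at weeks 12 and 16, for example by ANCOVA or a mixed model over the visits with a group-by-time term, adjusted for baseline value, age, sex and centre. Report the estimated difference with a 95% CI. Give within-arm kg and cm changes as descriptive means without p-values, and say that they are not evidence of improvement.

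No new visits, measurements or children are needed: weight, height and arm circumference are scheduled at every visit, and age and sex are already covariates for the primary analysis. The cost is a documented amendment with ethics approval, dated before analysis, plus modest analysis work. Z scores are less familiar to some readers, so the raw means should appear beside them.
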